#### Safety assessments

Safety will be assessed by renal function tests, liver function tests, routine blood tests, routine urine tests, routine stool tests, and electrocardiograms. These indicators will be detected at baseline (before treatment) and during the 4th week of the intervention.

### Participant timeline {13}

Details of the case distribution, specific measurements, and time points of data capture can be found in the SPIRIT Figure (Fig. 3).

**Fig. 3 Fig3:**
[figure not shown]
Details of measurements, and time points of data collection. EA, electroacupuncture; SZRD, Suanzaoren decoction; PSQI, Pittsburgh Sleep Quality Index; PSG, polysomnography; ISI, Insomnia Severity Index; NIHSS, National Institutes of Health Stroke Scale; HADS, Hospital Anxiety and Depression Scale; MRI, brain magnetic resonance imaging; fMRI, functional magnetic resonance imaging; MLT, nocturnal concentration of melatonin

### Sample size {14}

PSQI scores will be presented as the primary outcome. The sample size was calculated based on changes in PSQI scores. Based on a previous study [35], the global PSQI score after 4 weeks of treatment was 9.21 ± 4.05 in the intervention group and 13.18 ± 4.32 in the control group. We used the following formula to calculate the sample size.

$$ {n}_1={n}_2=\frac{{\left({Z}_{\alpha }+{Z}_{\beta}\right)}^2\ast 2{\sigma}^2}{\delta^2} $$

On the basis of 0.9 power to detect a significant difference (α = 0.05, two-sided), 25 participants are required for each group. Allowing for a 20% drop-out rate, a sample size of 30 for each group is needed. To improve the RCT quality and reduce the bias, we decided to recruit a sample size of 60 for each group. As a result, we plan to recruit a total of 240 patients for the whole trial.

### Recruitment {15}

Patients with post-stroke insomnia will be recruited through advertisements on the WeChat official platform and hospital bulletin boards. If patients are interested in this study, the research coordinator will obtain their contact details. Then, the principal investigator will make an appointment with each successive patient. In an individual room, the potential participant will be told in detail of the purpose and content of the study as well as the benefits and risks of participating by the principal investigator, who will screen them based on the inclusion and exclusion criteria and obtain informed consent from the eligible patients.

## Assignment of interventions: allocation

### Sequence generation {16a}

The investigator at Yichang Hospital of Traditional Chinese Medicine will generate random numbers 001–240 by SPSS 20.0 software (SPSS Inc., Chicago, IL, USA) and places random numbers in a sequenced, sealed, opaque envelope.

### Concealment mechanism {16b}

The random numbers in the sequenced sealed opaque envelopes will have been equally allocated to the four groups (0, 1, 2, or 3 group). The principal investigator, who will enrol the eligible patients, will open the envelopes based on patients’ registration order numbers and then assign the patients to groups 0, 1, 2, or 3 in accordance with the group number in the envelope. The random numbers will be placed in opaque sealed envelopes to prevent selection bias. The researchers, data collection staff, and data analysts will be blinded in the course of the random allocation sequence to avoid detection bias.

### Implementation {16c}

The designated investigator will generate the allocation sequence, and another investigator designated by the project leader will enrol and assign participants.

## Assignment of interventions: blinding

### Who will be blinded {17a}

We designed a single-blind trial in which the participants of the EA group, the participants of the sham EA group, data collection staff, and data analysts will be blinded during the course of the research. Because of the particular treatment manipulations, blinding the acupuncturists, the participants of the EA & SZRD group, and the SZRD group is impossible. During the trial process, acupuncturists and data collection staff will be forbidden to exchange information with each other and communicate with the study patients. We will conduct each treatment in a closed unit with patients wearing eye masks. To maximize blinding of participants, a sham device will be utilized [36, 37] (shown in Fig. 2A).

### Procedure for unblinding if needed {17b}

Researchers will be permitted to be unblinded in some specific situations, such as participants experiencing serious adverse events or disease progression, and where prompt treatment and appropriate management are needed. The procedure for unblinding will be as follows: (1) prior to unblinding, the researcher will need to inform the trial steering committee. (2) The researcher should unblind the intervention information of the patient based on the emergency envelope. (3) The researcher will need to fill out the report form of unblinding and note it on the case report form (CRF).

## Data collection and management

### Plans for assessment and collection of outcomes {18a}

All data will be documented in detail in the CRF after face-to-face visits. The same researcher will be responsible for the examination of each patient at each assessment. Baseline measurements, medical history, demographics, and previous medications will be collected at the first visit. The primary and secondary outcomes will be assessed at baseline (before treatment) and during the 2nd and 4th weeks of the intervention, as well as at the 8th and 12th weeks of follow-up. Safety assessments will be evaluated at baseline and during the 4th week of the intervention.

### Plans to promote participant retention and complete follow-up {18b}

Follow-up telephone calls and messages on the WeChat public platform will be conducted to promote participant retention.

### Data management {19}

Epidata 3.1 (EpiData Association, Denmark), which is a statistical package, will be used for data entry. Two trained data entry staff members will recheck the CRF and then independently perform data entry. The administrators at Medical College of China Three Gorges University will independently check and judge the input data and confirm whether all CRFs are being completed in a timely manner to ensure that the withdrawal of participants and all adverse events are recorded in CRFs.

### Confidentiality {27}

Patient names in the dataset will be identified with Pinyin initials and numbers. CRFs will be stored in a securely locked location. Epidata 3.1 will be locked and analysed by an independent statistician under the supervision of the administrators. The data and relevant records from this trial will be input on the ResMan Research Manager website at http://www.medresman.org.cn/login.aspx.

### Plans for collection, laboratory evaluation, and storage of biological specimens for genetic or molecular analysis in this trial/future use {33}

No biological specimens will be collected in this trial.

## Statistical methods

### Statistical methods for primary and secondary outcomes {20a}

Based on a previous study, the minimal clinically important difference is approximately 1.14–1.75 points on the PSQI score following treatments [38]. We will assume a treatment response with a score reduction on the PSQI of 2 or more points. Descriptive statistics will be used to analyse baseline characteristics for each group. Repeated measures analysis will be performed to make comparisons between the treatment groups and the control group (EA & SZRD versus sham EA, EA versus sham EA, and SZRD versus sham EA) at different time points (2nd, 4th, 8th, and 12th weeks). If a significant difference is detected, the next step will be to make comparisons among the three treatment groups in effectiveness. The Bonferroni correction method will be used for multiple comparisons. The Kruskal-Wallis test will be used for the analysis of data with a skewed distribution. Analysis of variance will be used for numerical variables, and the chi-squared test will be used for categorical variables. SPSS 20.0 software (SPSS Inc., Chicago, IL, USA) will be used to analyse the data.

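### The plan does not say that baseline PSQI enters the primary repeated measures analysis, and it sends skewed data to a rank test that can use neither baseline nor repeated visits

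*Protocol article*

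**What the plan says.** Section {20a} of the protocol article covers primary and secondary outcomes together. It states: "Repeated measures analysis will be performed to make comparisons between the treatment groups and the control group". The comparisons are each active arm against sham at weeks 2, 4, 8 and 12. If a difference is found, the three active arms are then compared with one another, with Bonferroni correction. No covariate is named, and the only stated use of baseline data is descriptive.

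The same section adds: "The Kruskal-Wallis test will be used for the analysis of data with a skewed distribution". It gives no criterion for skewness and does not exempt the primary outcomes. It also quotes a minimal clinically important difference of 1.14–1.75 PSQI points and sets treatment response at a reduction of 2 points or more.

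The PSQI entry in section {12} schedules the scale at baseline and weeks 4, 8 and 12. The polysomnography entry has one night at baseline and one at week 4.

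Section {14} says "The sample size was calculated based on changes in PSQI scores". The inputs it then gives are post-treatment values: "9.21 ± 4.05 in the intervention group and 13.18 ± 4.32 in the control group".

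**The concern.** Three features of the text leave the primary PSQI analysis open or weaken it.

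- **Baseline.** PSQI is measured in everyone before treatment, yet nothing says that the measurement is used in the model. A baseline score that correlates with the follow-up score removes variance from the arm comparison at no cost.
- **Outcome scale.** Section {14} says changes but uses post-treatment scores, and section {20a} does not say which is analysed. The two have different variances, so the choice affects precision.
- **Rank test.** Followed as written, the skewness rule makes the test depend on the observed distribution, with no threshold fixed beforehand. Kruskal-Wallis takes no covariate, does not use the visit structure, tests all arms at once and gives no estimate in PSQI points to set against the 1.14–1.75 range. A bounded 0–21 score and polysomnographic latencies can plausibly be skewed, so the rule may well be triggered.

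The stated aim is to compare the combination with each single therapy. Differences there may be smaller than the intervention-versus-control difference used for sizing, so precision matters most in those contrasts.

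**Working it through.** **Inputs from the protocol.** Two-sided alpha 0.05; power 0.90; week-4 means 13.18 and 9.21, a difference of 3.97; SDs 4.05 and 4.32; 60 recruited per arm; 20% drop-out.

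**Assumption.** The baseline to week-4 correlation ρ is not given. The range 0.3–0.7 is used.

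**Step 1: reproduce the plan's figure.** The plan's formula is n = 2σ²(z₁₋α/₂ + z₁₋β)²/δ².

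- σ = 4.32: n = 24.88, so 25, the stated figure.
- Pooled σ = √[(4.05² + 4.32²)/2] = 4.187: n = 23.38, so 24.

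The stated 25 therefore comes from post-treatment scores with no baseline term.

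**Step 2: does the scale matter?** For 3.97 points at 90% power with pooled SD, and equal SDs at baseline and follow-up for the change score, n per group is:

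| Analysis | SD used | ρ = 0.3 | ρ = 0.5 | ρ = 0.7 |
|---|---|---|---|---|
| Post-treatment score | σ | 24 | 24 | 24 |
| Change score | σ√[2(1−ρ)] | 33 | 24 | 15 |
| Baseline-adjusted | σ√(1−ρ²) | 22 | 18 | 12 |

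Change scores lose precision when ρ is below 0.5. Adjustment does at least as well as either alternative throughout.

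**Step 3: gain at the planned size.** Evaluable per arm: 60 × 0.8 = 48. Standard error of the difference without adjustment: 4.187 × √(2/48) = 0.855. Power is approximately Φ(δ/SE − 1.96); with adjustment SE is multiplied by √(1−ρ²).

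| Quantity | Unadjusted | ρ = 0.3 | ρ = 0.5 | ρ = 0.7 |
|---|---|---|---|---|
| Variance reduction (ρ²) | – | 9% | 25% | 49% |
| Power, 2.0 points | 65% | 69% | 77% | 91% |
| Power, 1.75 points | 54% | 57% | 66% | 82% |
| Difference detectable at 90% power | 2.77 | 2.64 | 2.40 | 1.98 |

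For 2.0 points unadjusted: 2/0.855 = 2.34; 2.34 − 1.96 = 0.38; Φ(0.38) = 0.65. For 3.97 points unadjusted: 3.97/0.855 = 4.64; 4.64 − 1.96 = 2.68; power 99.6%. Adjusted power there is at least 99.8%.

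**Step 4: allow for Bonferroni.** The number of comparisons is not fixed. If it is three, alpha is 0.05/3 = 0.0167 and the critical value is 2.394. Power for 2 points is then Φ(2.340 − 2.394) = 48% unadjusted. It is Φ(2.453 − 2.394) = 52% at ρ = 0.3 and Φ(3.277 − 2.394) = 81% at ρ = 0.7. The level falls, but the ordering is unchanged.

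**Step 5: what the rank test costs.** With normal data its asymptotic efficiency relative to the F test is 3/π = 0.955, so ranking itself costs little. The loss lies in the baseline, the repeated visits and the estimate in points, none of which it carries.

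**The case against.** The strongest objection is that the document never excludes baseline. A repeated measures analysis can hold baseline as a covariate or as a first level with group-by-time contrasts. It can also be run on change, which would fit the wording of section {14} and the response definition in section {20a}. The article condenses a fuller protocol, and covariate lists are often left to an analysis plan that is not shown. This stands. A reader might infer that baseline PSQI is left out of the model, but the text is only silent on it.

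A reader might also infer that chance baseline imbalance biases the result, since no stratification is described. It does not. Under randomisation the unadjusted comparison is unbiased, and its standard error already reflects chance imbalance.

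On size, the 2-point figure is the plan's within-patient response threshold, not a between-arm design difference; the correlation is assumed; and Step 3 uses one visit at alpha 0.05. These limits also stand, so the power figures are illustrations.

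On the rank test, the sentence sits in a list of tests by data type and does not name PSQI. The rule is written in advance, and the data analysts are to be blinded, which limits the room for choice. This carries less weight. The section heading covers the primary outcomes, nothing exempts them, and blinding does not supply the missing criterion or an estimate in points. The rule is also stated text, so an unseen analysis plan does not dispose of it.

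**Conclusion.** The point holds as one of specification and precision. The protocol does not state that baseline PSQI enters the primary analysis, is inconsistent on change versus post-treatment score, and fixes an unadjusted rank test for skewed data without a criterion or an exemption for primary outcomes.

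The size depends on ρ, which the document does not give. Over the assumed range the benefit runs from small to substantial for differences near 2 points. It is negligible for the 3.97-point design difference, so a reading that the trial is underpowered for its own design difference is not supported. No expected difference is given for combination versus single therapy, so power for those contrasts cannot be stated. The change is a worthwhile improvement at no data cost; it does not correct an invalid analysis.

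**What to change.** In section {20a}:

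1. Prespecify one longitudinal model for PSQI at weeks 4, 8 and 12, the visits that section {12} schedules, with arm, visit, arm-by-visit and baseline PSQI. Week 2 should not be listed for PSQI, because its own entry has no assessment then.
2. Report the arm contrasts as differences in PSQI points with confidence intervals, keeping the planned Bonferroni correction.
3. Use ANCOVA with the baseline value for the polysomnography measures, which have a single follow-up night.
4. Keep these models whatever the distribution. Use robust or bootstrap intervals if residuals are skewed, and make any Kruskal-Wallis test a sensitivity analysis only.

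In section {14}, describe the sizing as based on post-treatment scores, which is what the inputs are.

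The cost is wording: no added patients, visits or measurements. Section {25} requires a change to the analyses to go to the ethics committee as a new protocol version. The change should be made before any outcome data are seen by arm.

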## Trial design {8}

The study is designed as a 12-week, single-centre, randomized, single-blind, controlled trial. Study participants will be included according to the inclusion and exclusion criteria. Before starting the treatment, all eligible patients will undergo a standard neuroimaging examination (brain magnetic resonance imaging and functional magnetic resonance imaging), a baseline evaluation of sleep quality, neurological deficits, anxiety and depression, and measurement of nocturnal melatonin concentrations. Then, subjects will be equally randomized into four groups: the EA group, SZRD group, EA & SZRD group, and sham group. Patients in the EA group and sham group will receive EA stimulation or sham EA every other day for 4 consecutive weeks for a total of 14 sessions. Patients in the SZRD group will only take SZRD granules orally twice a day for 4 consecutive weeks. Patients in the EA & SZRD group will be administrated SZRD granules orally twice a day for 4 consecutive weeks, combined with EA stimulation every other day for 4 consecutive weeks, for a total of 14 sessions. Assessments will be carried out at baseline (before treatment), during the 2nd and 4th weeks of the intervention, and at the 8th and 12th weeks of follow-up.

The trial will be performed according to the principles of the Declaration of Helsinki (Fortaleza version, 2013), the Consolidated Standards of Reporting Trials [22], the Standards for Reporting Interventions in Clinical Trials of Acupuncture [23], and Recommendations for Intervention Trials (SPIRIT) Checklist.

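### Plain Bonferroni is valid for the six group comparisons, but Holm's step-down rule over the same six would keep the 5% error rate and never reject less

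*Protocol article*

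**What the plan says.** The section on statistical methods for primary and secondary outcomes {20a} of the protocol article sets out two steps. The first compares each active arm with sham: "EA & SZRD versus sham EA, EA versus sham EA, and SZRD versus sham EA". The second depends on the first: "If a significant difference is detected, the next step will be to make comparisons among the three treatment groups in effectiveness". With three active arms, that is three more pairwise contrasts and six in all. The adjustment is given in one sentence: "The Bonferroni correction method will be used for multiple comparisons". The article names no step-down variant. It does not say whether the divisor is three (within each step) or six (across both).

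The Sample size section {14} takes its one effect from a previous study, "9.21 ± 4.05 in the intervention group and 13.18 ± 4.32 in the control group", and concludes: "On the basis of 0.9 power to detect a significant difference (α = 0.05, two-sided), 25 participants are required for each group". It then adds "Allowing for a 20% drop-out rate, a sample size of 30 for each group is needed", and finally "we decided to recruit a sample size of 60 for each group". Allocation is equal (Trial design {8}): "subjects will be equally randomized into four groups".

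**The concern.** Bonferroni holds every contrast to the same strict level, whatever the other contrasts show. Holm orders the p-values and relaxes the level after each rejection. Over six contrasts the levels are 0.05/6, 0.05/5, and so on up to 0.05. It needs no assumption about how the tests are correlated, so the shared sham arm does no harm. It cannot lose a rejection that Bonferroni over the same family would make.

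The trial's aim is to show that the combination beats each single therapy. If that is true, EA and SZRD each differ from sham by less than the combination does. A step-down rule helps most in that pattern: one large contrast is rejected early and the smaller ones are then tested less strictly. What is at stake is some power for the smaller contrasts, without recruiting more patients.

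**Working it through.** **1. The plan's own sample size.** With δ = 13.18 − 9.21 = 3.97, two-sided α = 0.05 and power 0.90, the stated formula gives n = (1.960 + 1.282)² × 2σ²/3.97². For σ = 4.32 this is 24.9, so 25 per group, as stated. (The pooled SD of 4.187 gives 24 and 4.05 gives 22.) No multiplicity adjustment enters. The 60 actually planned less 20% leaves 60 × 0.8 = 48 evaluable.

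**2. Bonferroni over six, in closed form.** The critical value at 0.05/6 two-sided is 2.638. The standard error of a difference is 4.32 × √(2/n): 0.882 at n = 48 and 0.789 at n = 60. The article gives no separate effects for EA, SZRD or the combination. The 2-point effect below is an assumption.
- Difference 2, n = 48: Φ(2/0.882 − 2.638) = Φ(−0.37) ≈ 35%.
- Difference 2, n = 60: Φ(2/0.789 − 2.638) = Φ(−0.10) ≈ 46%.
- Difference 3.97, n = 48: Φ(3.97/0.882 − 2.638) = Φ(1.86) ≈ 97%.

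**3. Holm over the same six, by simulation.** The model has four arms with normal means, a shared sham arm, SD 4.32, z tests, one time point and 300,000 trials per scenario.

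| True differences from sham (combination / EA / SZRD) | n per arm | Each single therapy v sham: Bonferroni ÷ 6 | Holm over six |
|---|---|---|---|
| 3.97 / 2 / 2 (assumed) | 48 | 35% | 42% |
| 3.97 / 2 / 2 (assumed) | 60 | 46% | 54% |
| 3.97 / 3.97 / 3.97 | 48 | 96.9% | 97.7% |
| 3.97 / 3.97 / 3.97 | 60 | 99.2% | 99.4% |

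In the 3.97/2/2 pattern the combination exceeds each single therapy by 3.97 − 2 = 1.97, so those contrasts gain about as much. With SD 4.187 and other weaker single-arm effects, the gain for a family of six ranged from about 1 to 13 points. Under the global null both rules gave a family-wise error of about 4.2%.

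**4. Holm separately within each set of three.** Suppose the combination and EA are both 3.97 better than sham and SZRD equals sham. There is then one true null in each set: SZRD v sham, and combination v EA. These two contrasts share no arm. Once the large contrasts are rejected, Holm tests the remaining null in each set at 0.05, so the chance of at least one error is near 1 − 0.95² = 9.75%. Simulation with the gate gives 9.4% (n = 48) and 9.7% (n = 60). Bonferroni by three in each set gives near 1 − (1 − 0.05/3)² = 3.3%, and simulation agrees (3.3-3.4%). If only the combination works, the figures are 8.2-8.5% with Holm per set and 4.4% with Bonferroni per set.

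**5. If Bonferroni by three in each gated set was meant.** In the 3.97/2/2 pattern that rule gives each single therapy v sham about 45% (n = 48) or 56% (n = 60), compared with 42% and 54% for Holm over six. Holm over six is therefore slightly weaker there. Four arms allow only 6, 3, 2, 1 or 0 true pairwise nulls, and the gate protects the case of six. This permits the step-down divisors 3, 3, 3, 3, 2, 1 (Shaffer) behind the gate. Simulated family-wise error stayed below 5% in every configuration run, and the gain over Bonferroni by three was only about 1 point per contrast.

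**The case against.** The strongest objection is that nothing here is wrong. Bonferroni controls the error rate, no other part of the article contradicts it, and it has simple matching simultaneous confidence intervals that Holm lacks. All of this stands. It makes the point an optional improvement.

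A reader might go further and infer that the plan forgoes 8 to 11 points of power that Holm would supply at no cost. The documents do not support that. A gain of that size comes from treating the three sham contrasts alone as the family and assuming patterns such as 3.97/2/2 (45% to 56% per single therapy at 48 per arm) or 2.5/2.5/2.5 (67% to 75%). The article gives neither pattern. Its 2-point response threshold is a score reduction within a patient, not a difference between groups. Even with Holm in each set of three, the combination-versus-single contrasts gain only about 3 points (43.5% to 46.3%). The change is not free either: with the plan's gate, that version roughly doubles or triples the error across the six comparisons (step 4 of the working).

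It is also fair to object that the family is inferred. The article does not fix the divisor, and under one reading Holm over six is not uniformly better.

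**Conclusion.** The point holds as a modest, optional gain in efficiency. If the plan's Bonferroni divides by six, Holm over those six is at least as powerful for every contrast with the same 5% guarantee. The gain is about 7 to 8 points for each single therapy against sham under the assumed 3.97/2/2 pattern, and under about 1 point if every active arm reaches 3.97. If the plan divides by three within each gated set, at most about 1 point can be recovered without exceeding 5%.

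The figures rest on normal data, SD 4.32 in every arm, 48 to 60 evaluable per arm and a single time point. Correlation between visits and testing at several visits are not modelled, because the article gives no inputs for them. The guarantee that Holm never rejects less than Bonferroni over the same family needs none of these assumptions.

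**What to change.** First state which family the correction covers.

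If it is all six comparisons, replace the Bonferroni sentence with: *The Holm step-down procedure at an overall two-sided 5% will be applied across all six pairwise comparisons of the four groups; Bonferroni-adjusted confidence intervals will be reported alongside.* Do not apply Holm at 5% separately within each set of three.

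If Bonferroni by three within each gated set was meant, either leave it or keep the gate and use the step-down divisors 3, 3, 3, 3, 2, 1.

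The cost is one sentence, fixed before group-level data are seen, and no extra patients. Because the article sends changes of analysis to the ethics committee as a new protocol version {25}, a submission may be needed. The remaining drawback is one of presentation: Holm has no simple matching simultaneous intervals, so a Bonferroni-adjusted interval may include zero for a contrast that Holm rejects. The report should say so.
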